**Figure 2 fig2:**
[figure not shown]
Follow-up plan.

During observation, investigators will detailly record the following events:

MACCPE (the occurrence time, special treatment and radiological data).Mortality (the occurrence time and cause of death).Neurological function outcome, which is evaluated by the mRS, GCS, and GOS.Intracranial re-hemorrhage or intracranial bleeding potentially related to aspirin (the occurrence time, treatment, radiological data and cause of bleeding).Regular follow-up head CT.

### Monitoring the effectiveness of antiplatelet therapy

Before and after aspirin administration, we will assess the platelet function. The platelet function will be assessed using the thromboelastogram (TEG). All parameters, including maximum amplitude (MA), citric acid kaolin (CK), reptilase (A), aspirin (AA), are recorded through standard tracing. Based on MA, the rate of platelet function inhibited by aspirin (AA%) was calculated using the formula as shown below:

$$AA\%=\frac{MA\left(CK\right)-MA\left(AA\right)}{MA\left(CK\right)-MA\left(A\right)}$$

For patients in the early start group, the platelet function will be detected before aspirin administration and 7 days after administration. AA% > 50 is defined as the good response to aspirin. Moreover, for the patients in the normal start group, because they do not receive any antiplatelet therapy, the platelet function assessment do not need to perform for these patients.

### Quality control of the research

To avoid participant bias and ensure a sufficient source of operated sSICH patients, we will enroll appropriate centers according to follow standards: (1) the medical centers cover at least two communities or work as a referral unit for hemorrhagic stroke; (2) the center can conduct various treatments for sSICH and can fully represent the diagnosis and treatment of sSICH at a national level; (3) the medical center treats at least 50 sSICH patients annually by surgical methods; (4) the center can complete all examinations which are required in the study. Finally, nine medical centers encounter our standards and participate in this study. This study will conduct in nine regional neurosurgical centers simultaneously.

In this study, operation decision is made based on the consensus of neurosurgeons and patient family, according to clinical guideline. The operation is performed by a senior neurosurgeon, working as a neurosurgeon for more than 10 years. After operation, all of the patients would receive standardized care according to the guidelines. Before and after operation, patient will receive blood pressure management, and the target blood pressure is <140/90 mmHg.

At statistical stage, we will review all postoperative treatments and further exclude: (1) the patients receiving non-indicated platelet transfusion or anticoagulation treatment; (2) the patients whose the postoperative blood pressure are abnormal even receiving special treatment; (3) the patients suffering from an abnormal change of blood cells, abnormal hypercoagulation or disseminated intravascular coagulation.

### Statistical analysis

#### Sample size

The sample size is estimated using the PASS 15 (PASS corporation, United States). In our preliminary study, we investigated the clinical characteristics and outcome of operated sSICH patients in Beijing Tiantan Hospital. The incidence of main adverse cardiovascular and cerebrovascular events was 10.8% after operation (Wu et al., 2021). The E-start study expects to reduce the incident of MACCE by 5%. Patients were randomized at a ratio of 1:1 to one of two groups. At (1 − β) as 0.8 and α as 0.05, 244 consecutive patients would be enrolled in this study (122 in the early start group and 122 in the normal start group). This study prepares to enroll 250 operated sSICH patients, including 125 subjects in the early start group and 125 subjects the normal start group.

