## Introduction

Severe spontaneous intracerebral hemorrhage (sSICH), characterized by a massive intracerebral hemorrhage and coma, is the most acute subtype of hemorrhagic stroke, with considerable disability and mortality (Cordonnier et al., 2018; Gross et al., 2019). Notably, sSICH patients are characterized by old age and usually have ischemic-arterial-related comorbidities (Wu et al., 2021). Although surgical treatment can improve the outcome and reduce the mortality of sSICH patients (Luzzi et al., 2019; Wu et al., 2021), they are still threatened by the risk of ischemic artery events postoperatively, e.g., major cardiovascular/cerebrovascular/peripheral vascular events (MACCPE; Kumar et al., 2010; Devereaux and Sessler, 2015; Smilowitz and Berger, 2016; Goshgarian and Gorelick, 2017; Smilowitz et al., 2017; Smilowitz and Berger, 2020).

In high-and middle-income countries, about a quarter of spontaneous intracerebral hemorrhage patients received antiplatelet therapy before hemorrhage (Lovelock et al., 2007). Moreover, for patients suffering from spontaneous intracerebral hemorrhage, ischemic artery events are the important factor related to the long-term poor outcome (Flynn et al., 2010; Pennlert et al., 2014; Poon et al., 2014; Casolla et al., 2019; Parasram et al., 2022). However, after hemorrhage, discontinuation of antiplatelet therapy, abnormal cardia-cerebrovascular hemodynamics and bedridden condition will certainly increase the risk of MACCPE (Devereaux and Sessler, 2015; Smilowitz and Berger, 2016; Goshgarian and Gorelick, 2017; Smilowitz et al., 2017; Ding et al., 2019; Smilowitz and Berger, 2020). Our previous study showed that approximately 20% sSICH patients had a history of antiplatelet therapy and ischemic artery events occurred in more 10% patients (Wu et al., 2021). The incident rate of MACCPE may be higher in the sSICH patients with high risk of ischemic artery events. Thus, timely and appropriate antiplatelet therapy may helpful to prevent the ischemic events and improve the outcome of sSICH patients.

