### Endpoints and relative definitions

The primary efficacy endpoint is the incidence of MACCPE after operation. The MACCPE event is identified when patients suffer from a new cerebral infarct outside the surgical area, enlarging cerebral infarction area, new-onset TIA, more frequent TIA, new-onset myocardial infarction, reperfusion therapy for original myocardial infarction, pulmonary embolism, or deep venous thrombosis.

The other outcomes included: (1) the 3-month mortality after surgery; (2) in-hospital mortality; (3) 30- and 90-day neurological function after operation, which is assessed using the modified Rankin scale (van Swieten et al., 1988) (mRS) or Glasgow outcome scale (Jennett and Bond, 1975; GOS).

The safety endpoint is the incidence of hemorrhagic complications during antiplatelet therapy, i.e., the radiological re-hemorrhage of the operative region (comparing with the preoperative or postoperative first images) or new occurrence of intracerebral hemorrhage, subdural hemorrhage, subarachnoid hemorrhage or intraventricular hemorrhage.

For the cerebral infarcts, immediate CT (due to sudden or continuously deteriorating neurological state) and regular follow-up CT (postoperative 7 ± 5 days, postoperative 90 ± 10 days) will screen new hypodense lesions. If new hypodense lesions are found, an MRI will be used to determine the lesions. New cerebral infarcts outside the surgical area were defined as new hypodense lesions on T2-weighted MRI, which are visible in at least two continuous views. Enlarging infarctions were defined as an increase in a previously existing area of T2-weighted signal hyperintensity of at least 3 mm in one dimension (Vendt et al., 2009).

Transient ischemic attack (TIA) was defined as a transient episode (duration of symptoms < 24 h) of neurological dysfunction caused by focal brain, spinal cord, or retinal ischemia without showing acute infarction on CT images. The primary endpoint was met if patients presented with new-onset TIA or more frequent TIA.

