##### Endpoint and outcome evaluation

We intend to check the plausibility and validity before the database is locked for analysis. We will exclude the cases that could influence the accuracy of conclusion. Patients who do not meet the requirement of quality control may be further excluded based on the consensus of investigators’ discussion.

Categorical variables are presented as numbers (no.) and percentage (%). Continuous variables with normal distribution are expressed as means and standard deviation, and medians and inter-quartile range (IQR) if otherwise. The differences between groups in continuous variables are compared by performing the student’s t-tests or Wilcoxon rank sum tests, and the differences in categorical variables are compared using the chi-square tests or Fisher’s exact tests. The incident rate (IR) of PR and its 95% confidence interval (CI) is calculated. The univariate and multivariate Cox regression analyses are performed in PR-related analysis. The result of Cox regression analysis is presented as hazard ratio (HR) and 95% CI. The statistical analyses are conducted with SPSS 24.0 (SPSS, Chicago, IL), with two-sided *p* < 0.05 considered of statistical significance.

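### 122 patients per arm gives about 30% power, not 80%, for the stated fall from 10.8% by 5 points, and the planning rate carries a different endpoint label

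*Protocol article*

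**What the plan says.** The Sample size section of the protocol article gives all the inputs to its calculation.

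- Control rate, from the sponsor's earlier study: "The incidence of main adverse cardiovascular and cerebrovascular events was 10.8% after operation".
- Effect: "The E-start study expects to reduce the incident of MACCE by 5"%.
- Allocation: "Patients were randomized at a ratio of 1:1 to one of two groups".
- Error rates: "At (1 − β) as 0.8 and α as 0.05".
- Result: "244 consecutive patients would be enrolled in this study (122 in the early start group and 122 in the normal start group"). Planned enrolment is then rounded up to 250, or 125 per arm. No dropout rate is given.

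The section on endpoint and outcome evaluation sets a two-sided 0.05 significance level and names chi-square or Fisher's exact tests for categorical variables.

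The section on endpoints and definitions states: "The primary efficacy endpoint is the incidence of MACCPE after operation". Pulmonary embolism and deep venous thrombosis both count as events. Of the population enrolled here, the Introduction says: "The incident rate of MACCPE may be higher in the sSICH patients with high risk of ischemic artery events".

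**The concern.** A fall from about 11% to about 6% is a small absolute difference between two low proportions, and 122 per arm is far fewer than such a difference usually needs. The article gives no other justification for the size of the trial on its primary endpoint.

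If the number is wrong, the trial claims a power it does not have. A non-significant result would then be the likely outcome even if early aspirin works exactly as hoped. Read against a claimed 80% power, it could be taken as evidence against early treatment.

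A second question is whether the 10.8% describes the endpoint and population of this trial at all.

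**Working it through.** **Inputs.** Control rate p1 = 0.108, power 0.80, alpha 0.05 and 1:1 allocation come from the Sample size section. The two-sided test comes from the section on endpoint and outcome evaluation. The 5% is read first as 5 percentage points, so p2 = 0.058.

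**Required size.** The pooled two-proportion formula, per arm, is

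n = [1.96·√(2·p̄(1−p̄)) + 0.8416·√(p1(1−p1) + p2(1−p2))]² / (p1−p2)², with p̄ = (p1+p2)/2 = 0.083.

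- First term: 1.96 × √(2 × 0.083 × 0.917) = 0.7647.
- Second term: 0.8416 × √(0.108 × 0.892 + 0.058 × 0.942) = 0.3270.
- n = (0.7647 + 0.3270)² / 0.05² = 476.7, so 477 per arm or 954 in total.

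The choice of method matters little. The unpooled variance gives 474 per arm, the arcsine method 468, and the continuity correction 516. A log-rank calculation gives about 904 (Schoenfeld) to 964 (Freedman) in total.

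**Attempts to reproduce 122 per arm:**

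| Reading of the 5% | Test | n per arm for 80% power | Power at 122 | Power at 125 |
|---|---|---|---|---|
| 10.8% to 5.8% | two-sided | 477 | 29.2% | 29.8% |
| 10.8% to 5.8% | one-sided | 376 | 40.9% | 41.6% |
| 10.8% to 5.0% | two-sided | 339 | 38.9% | 39.7% |
| 10.8% to 5.0% | one-sided | 267 | 51.4% | 52.2% |
| 5% relative, to 10.26% | two-sided | about 50,700 | 3.4% | 3.4% |

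None gives 122.

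**Power at the planned size.** Power = Φ{[(p1−p2)√n − 1.96·√(2p̄(1−p̄))] / √(p1(1−p1) + p2(1−p2))}.

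- At n = 122 this is Φ(−0.547) = 0.292.
- At n = 125 it is Φ(−0.529) = 0.298.
- Exact enumeration for the chi-square test gives 29.0% and 29.8%. For Fisher's exact test it gives 21.2% and 21.9%.

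**What 125 per arm can detect.** Solving the same expression for 80% power with p1 = 0.108 gives p2 ≈ 0.021. That is a drop of 8.7 points, or a relative reduction of about 80% (8.7/10.8). At 122 per arm, p2 ≈ 0.020.

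**Event count, since Cox regression is also mentioned.** The implied hazard ratio is ln(0.942)/ln(0.892) = 0.523. Schoenfeld's formula needs 4(1.96 + 0.8416)²/(ln 0.523)² ≈ 75 events. The plan's own rates yield 125 × (0.108 + 0.058) ≈ 21.

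**Other control rates (assumptions, at 125 per arm):**

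| Control rate | Power, fixed 5-point drop | Power, same relative reduction (46%) |
|---|---|---|
| 15% | 22% | 40% |
| 20% | 18% | 53% |
| 25% | 16% | 64% |

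None reaches 80%. At a 20% control rate, the same relative reduction would still need about 237 per arm.

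**Endpoint and population.** The 10.8% is called MACCE and refers to operated patients. The Introduction describes the earlier study's result as ischaemic artery events in just over 10%. The trial's endpoint is MACCPE, which counts venous events. It is measured in patients chosen for high risk, after those with an event in the first 3 days are set aside (Patient selection).

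**The case against.** The arithmetic has no good answer, but several points on the other side deserve weight.

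- **Non-inferiority.** Two set-ups come close to 122. A 5-point margin with a true 5-point benefit at one-sided 0.025 needs 119 per arm. A 10-point margin with equal rates at one-sided 0.05 needs 120. Both require a margin that the article never states, and its stated aim is a reduction in events. They do not explain the figure, though the claim is properly limited to superiority readings.
- **Higher risk in this population.** The Introduction anticipates a higher rate. If the relative reduction held, power would be better than 30%, but it stays below 80% at the assumed rates of 15% to 25%. If the 5-point drop held, power would be worse. The range belongs in the corrected text.
- **Endpoint label.** The earlier study's event definition is not shown. The Sample size section uses MACCE for this trial's own target too, so loose naming is possible. What stands is that label and population differ on the text. The effect on the rate cannot be computed.
- **Early events.** The Discussion reports that MACCPE in the SAP-ICH cohort starts about day 4 and peaks on day 7. The 3-day exclusion probably removes few events.
- **Fisher's test.** With about 10 events expected per arm, chi-square would normally apply, so about 30% is the figure to use rather than 22%.

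**Conclusion.** The sample-size statement is wrong as written. On the article's own inputs and a two-sided test, 80% power needs about 477 per arm, roughly 3.9 times the stated 122. Power at the planned 125 per arm is about 30%. The most favourable two-sided reading, a fall to 5%, gives about 40%.

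This rests on reading the 5% as percentage points, which is the natural reading, and on no losses. The six extra patients cover only 6/250 = 2.4%. The sections on quality control and on endpoint and outcome evaluation allow further exclusions at the analysis stage, which would lower power again.

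The mismatch between the planning rate and the endpoint is real on the text but secondary, and its size is unknown. The arithmetic fails without it.

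**What to change.** 1. Replace the power statement, for example: With 125 patients per arm and a two-sided alpha of 0.05, power is about 30% for 10.8% versus 5.8%; 80% power is reached only for about 10.8% versus 2.1%. State that the 5% means percentage points.
2. Re-derive the control rate for the actual endpoint (MACCPE after day 3 in high-risk patients) from the SAP-ICH cohort, which the sponsor has already analysed for event timing. Use one endpoint name throughout. Until that rate is available, give power over a range of control rates, as in the second table above.
3. State that the result will be read from the effect estimate and its 95% confidence interval, and that p ≥ 0.05 will not be taken as evidence of no effect.

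The cost is protocol and analysis-plan wording plus a look at existing cohort data. No extra patients are needed, but the stated power becomes much less favourable. If the sponsor wants to keep the 80% claim for a 5-point drop, the alternative is about 954 patients at a 10.8% control rate. The article does not say whether that is feasible.

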##### Endpoint and outcome evaluation

We intend to check the plausibility and validity before the database is locked for analysis. We will exclude the cases that could influence the accuracy of conclusion. Patients who do not meet the requirement of quality control may be further excluded based on the consensus of investigators’ discussion.

Categorical variables are presented as numbers (no.) and percentage (%). Continuous variables with normal distribution are expressed as means and standard deviation, and medians and inter-quartile range (IQR) if otherwise. The differences between groups in continuous variables are compared by performing the student’s t-tests or Wilcoxon rank sum tests, and the differences in categorical variables are compared using the chi-square tests or Fisher’s exact tests. The incident rate (IR) of PR and its 95% confidence interval (CI) is calculated. The univariate and multivariate Cox regression analyses are performed in PR-related analysis. The result of Cox regression analysis is presented as hazard ratio (HR) and 95% CI. The statistical analyses are conducted with SPSS 24.0 (SPSS, Chicago, IL), with two-sided *p* < 0.05 considered of statistical significance.

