#### Step 3: Outcome evaluation

During hospital stay, patients will receive a series of special examinations of MACCPE at 10 ± 4 days after administration of aspirin, in order to identify whether there is an occurrence of MACCPE. If patients have a sudden unconsciousness, or suddenly or gradually worsening neurological states after administration of aspirin, a head CT examination will be conducted immediately to identify whether there is an occurrence of re-hemorrhage. If the patient occurs ischemic events, the antiplatelet or anticoagulation therapy will be added to the patient based on the specific condition. These patients meet the endpoint when ischemic events occur, so they will not be excluded from this study.

Patients will be regularly followed up at 30 and 90 days. To the patient who did not discharge in 30 days, we would assess the clinic score at the bedside. To the discharged patient, we assess the clinic score *via* outpatient or phone review. At 90 days, if the patient could not complete the follow-up examination in the medical centers involved to the study, they will be required to complete the relative examinations in the local hospitals. Our investigators will ask patients’ family members to upload the follow-up data and assess the quality of these data. If these data are out of required quality and more details could not be got, the patients will be considered as the patients withdrawing from the follow-up (Figure 2).

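### Randomised patients are to be excluded at the analysis stage on open-ended or endpoint-related grounds, with no blinding of those decisions stated, which can bias both the MACCPE and the re-hemorrhage comparison

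*Protocol article*

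**What the plan says.** Two sections of the protocol article prescribe exclusions.

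- **Quality control of the research:** "At statistical stage, we will review all postoperative treatments and further exclude". Three groups follow. The first is anyone given platelets or an anticoagulant without an indication. The second is anyone whose pressure after surgery stays out of range despite being treated for it. The third is worded as "the patients suffering from an abnormal change of blood cells, abnormal hypercoagulation or disseminated intravascular coagulation".
- **Statistical analysis, Endpoint and outcome evaluation:** after announcing a plausibility and validity check before database lock, it says "We will exclude the cases that could influence the accuracy of conclusion". A consensus route is added for those failing quality control, who "may be further excluded based on the consensus of investigators" in discussion.

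The quality-control rules and the first statistical sentence say *will*; the consensus sentence says *may*.

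Three other places bear on the point:

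- Study design describes open-label treatment with blinded endpoint assessment. Endpoints and relative definitions applies that blinding to the two investigators who assess MACCPE and re-hemorrhage.
- Table 3 places randomisation at 3 days.
- Step 3 (Outcome evaluation) says that patients who have an ischemic event, and are given added therapy for it, have met the endpoint and stay in the study.

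The article names no analysis of all randomised patients in the arm assigned.

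**The concern.** Randomisation makes the arms comparable at day 3. An exclusion made later preserves that only if it depends on facts fixed before randomisation, or on facts related to neither arm nor outcome, and is decided without knowledge of either. The rules here do not guarantee this.

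The three quality-control criteria concern the postoperative course and carry no date limit, so they take in what happens after aspirin is started or withheld. Several sit near the endpoints. Hypercoagulation is close to deep venous thrombosis and pulmonary embolism, which are MACCPE components. Platelet transfusion, uncontrolled pressure and disseminated intravascular coagulation are close to re-hemorrhage. Whether a transfusion or anticoagulant was indicated is a judgement. The accuracy-of-conclusion rule has no criterion at all.

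At stake are the primary efficacy result and the safety result. Each would be computed on a subset whose membership may depend on treatment and outcome.

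This is not a matter of detail left to an analysis plan. The exclusions are stated affirmatively, and an analysis plan could remove the problem only by departing from the published text.

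**Working it through.** **1. Side by side.** Randomisation is at day 3, and the quality-control review takes place at the statistical stage. Whoever it removes has therefore already been randomised, whatever the date of the finding that triggers removal. The triggering finding may fall on days 0–3 or later; the text does not say. A patient with deep venous thrombosis and abnormal hypercoagulation is kept by Step 3 and excluded by the third quality-control rule. A patient with re-hemorrhage and uncontrolled pressure is excluded by the second rule, and nothing retains that patient.

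**2. Inputs for an illustration.** The plan gives no expected number of exclusions, so there is no figure of its own to reproduce. From Sample size: control rate 10.8%, 125 per arm, and a reduction by 5%, read here as absolute (an assumption), giving 5.8%. Expected events are 125 × 0.108 = 13.5 and 125 × 0.058 = 7.25, about 21 in all, rounded to 14 and 7. The plan allows chi-square or Fisher's exact test, two-sided at 0.05.

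**3. Test.** z = (p₂ − p₁) / √[p(1 − p)(1/n₁ + 1/n₂)], with p the pooled proportion.

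- No exclusions, 7/125 vs 14/125: p = 21/250 = 0.084; z = 0.056/√(0.084 × 0.916 × 0.016) = 0.056/0.0351 = 1.60.
- Three early-start patients with events removed, 4/122 vs 14/125: p = 18/247 = 0.0729; z = 0.0792/0.0331 = 2.39.

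| Early start vs normal start | Removed | Chi-square | Yates | Fisher |
|---|---|---|---|---|
| 7/125 vs 14/125 | none | 0.11 | 0.17 | 0.17 |
| 5/123 vs 14/125 | 2 early-start with events | 0.035 | 0.061 | 0.054 |
| 4/122 vs 14/125 | 3 early-start with events | 0.017 | 0.032 | 0.025 |

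Removing two crosses 0.05 only with the uncorrected chi-square. Removing three crosses it with all three tests.

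**4. The other direction.** Removing control events from 7 vs 14 only takes a non-significant result further away: 7/125 vs 11/122 gives p = 0.30. To see significance lost, a different start is needed. 7/125 vs 17/125 gives chi-square p = 0.032, and removing two control patients with events (7/125 vs 15/123) gives 0.068. By Fisher that start is already just above 0.05 (0.052).

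**5. Exclusions that need not matter.** Removing events equally from both arms does not cross 0.05: 6/124 vs 13/124 gives 0.095, and 5/123 vs 12/123 gives 0.078. Removing three early-start patients without events (7/122 vs 14/125) gives 0.12.

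**6. Bias with no true effect.** Let both arms have rate π = 0.108, and let each early-start patient with an event be excluded with probability q. The observed early-start rate is π(1 − q)/(1 − πq).

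- q = 0.2: 0.0864/0.9784 = 8.8%
- q = 0.3: 0.0756/0.9676 = 7.8%

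Apparent reductions of 2.0 and 3.0 points thus arise from exclusion alone. Exact enumeration of the two-sided type I error (uncorrected test, 125 randomised per arm) gives 0.050 at q = 0, 0.057 at 0.1, 0.081 at 0.2 and 0.125 at 0.3. The average numbers removed are 0, 1.4, 2.7 and 4.1. The values of q are assumptions shown as a range.

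**The case against.** The strongest reply is that the plan already protects the endpoint. Step 3 retains patients with ischemic events, and the first quality-control rule reaches only non-indicated transfusion or anticoagulation, so treatment given for an endpoint event arguably falls outside it. The illustration removes the very patients Step 3 keeps. This has weight for the transfusion and anticoagulation rule. But the Step 3 sentence addresses added therapy after an ischemic event. It does not clearly override the blood-pressure and coagulation rules or the open-ended one, and it says nothing about re-hemorrhage.

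A second reply is that the check before database lock is ordinary data cleaning. Plausibility checks may be, but excluding patients for their clinical course is not, and locking the database later does not make the decision blind.

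Some stronger readings are tempting and go beyond the text:

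- *The excluders know the arm.* Masking of these decisions is unspecified. The trial is open-label, but the article does not say who sits in the consensus discussion or what they can see.
- *Every criterion is a post-randomisation event.* The rules say postoperative and are undated, so findings on days 0–3 may be included.
- *Inadequate 90-day uploads are another exclusion route.* The text says "the patients will be considered as the patients withdrawing from the follow-up", which is loss to follow-up and not deletion from the analysis.
- *The margin between 244 and 250 patients leaves no room for exclusions.* That is a sample-size question and does not bear on whether the exclusions bias the comparison.
- *Two or three exclusions will decide the trial.* They could, if they all fall on patients with events in one arm. The documents give no exclusion rate.

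**Conclusion.** The point stands. As written, the plan removes randomised patients from the analysis on grounds that may depend on treatment and outcome, without stated blinding and, in one rule, without any criterion. It can bias both MACCPE and re-hemorrhage, and the direction cannot be determined from the documents.

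The size is illustrative. With about 21 expected MACCPE events, selective removal of three patients out of 250 (1.2%) can move p from 0.11 to 0.017 (Fisher 0.025); with two, the answer depends on the test. This assumes an absolute reduction of 5 points, rounded event counts, and exclusions confined to early-start patients with events, which is a one-directional worst case. Balanced exclusions of the same number of events do not cross 0.05. No size can be put on the safety comparison, because the article gives no expected re-hemorrhage rate. The need for correction rests on the exclusion rules themselves, not on these p-values.

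**What to change.** 1. State that the primary analyses of MACCPE and of re-hemorrhage include all randomised patients in the arm assigned.
2. Delete the accuracy-of-conclusion exclusion and the exclusions by investigators' consensus. Implausible values found before lock should be queried and corrected, with the patient kept.
3. Use the three quality-control criteria only to define a per-protocol sensitivity set, with objective definitions and a stated time window, decided blind to arm and outcome before database lock.
4. Reconcile the Step 3 retention sentence with the quality-control and statistical sections, so that retention covers re-hemorrhage as well as ischemic events.

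The cost is a change of wording and one extra sensitivity analysis. No additional patients, visits or data are needed.
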